**Table 1 tbl1:**
[figure not shown]

[figure not shown]
Summary of enrolment, intervention, and assessments, including all outcome measures [31].

#### Co-primary outcomes: physical functioning and physical activity

2.5.1

The co-primary outcomes are physical functioning and physical activity (i.e., average steps per day over 7 days).

Physical functioning will be measured using the RMDQ [32]. This is the most important domain in the core outcome set for LBP [33]. The RMDQ is a 24-item self-report questionnaire about how LBP affects functional activities. Each question is worth one point so scores can range from 0 (no disability) to 24 (severe disability). The RMDQ is a reliable tool to measure the impact of LBP on physical functioning [34].

Physical activity will be assessed with the activPAL activity monitor (activPAL4, PAL Technologies LTD., Glasgow, U.K.) [35]. The activPAL measures physical activity and sedentary time through measuring accelerations and posture of the thigh [36]. The activPAL is a small non-invasive electronic logging device designed to quantify free-living daily activities. Participants follow a nine-day wear protocol, where the device will be worn consecutively, except during water-based activities (i.e., taking a bath, swimming). Excluding attachment and removal days, the device will be worn for 24 h for seven consecutive days at four time points (baseline and 12, 24 and 36 months).

#### Secondary outcomes

2.5.2

Secondary outcomes will be assessed at the five main time points (baseline and 6, 12, 24 and 36 months) and include LBP intensity (NPRS), habitual food intake (FFQ), sleep habits (PSQI), quality of life (EQ5D5L), global perceived effect (GPE), systemic inflammation markers, and height and weight [[37], [38], [39], [40], [41]]. Pain beliefs (B-IPQ), pain self-efficacy (PSEQ) and fear of movement (TSK) will only be assessed at baseline [[42], [43], [44]]. An overview of all secondary outcomes is provided in Table 1.

#### Cost-effectiveness

2.5.3

Cost-effectiveness of the intervention will be evaluated against usual care over 36 months. Costs will be measured from a societal and a healthcare perspective. From the societal perspective, costs will include the cost of the intervention, other healthcare use (i.e., primary, secondary, tertiary and medication), informal care, sports memberships and equipment, as well as the cost of productivity losses from paid (i.e., absenteeism and presenteeism) and unpaid work (e.g., voluntary work). From a healthcare perspective, only costs accruing to the formal Dutch healthcare sector will be included. Intervention costs will be estimated using micro-costing, which involves collecting detailed information on the quantity of resources used as part of the intervention (e.g., number of physiotherapy sessions) and their corresponding unit costs. Data on all other kinds of resource use will be obtained via iMTA-based cost questionnaires [45], tailored to the specific patient population and intervention. Resource use will be valued in accordance with the Dutch manual of Costing [46]. Quality-adjusted life years (QALYs) will be derived from the EQ-5D-5L. The EQ-5D-5L health states will be translated into utility values using the Dutch value set, with scores anchored at 0 (equivalent to death) to 1 (full health) [47]. QALYs will be computed by multiplying the duration spent in each health state by its associated utility value. Both questionnaires will be administered at baseline and at 3, 6, 9, 12, 18, 24, 30, and 36 months.

#### Process evaluation

2.5.4

The process evaluation will study the implementation and mechanism of impact of the intervention, and will be carried out alongside the RCT with a mixed-methods approach using the UK MRC guidelines for process evaluation for complex interventions [48]. Both participants and physio therapists will be asked to complete questionnaires at baseline, 6 and 24 months. A selection of participants will be invited to join a focus group, and a selection of physio therapists will be invited for a semi structured interview about their experiences during the intervention, at 6 and 24 months. A trained independent researcher will conduct the focus groups and interviews. An overview of research aims and data collection is shown in Table 2.

**Table 2 tbl2:**
[figure not shown]

[figure not shown]

[figure not shown]

[figure not shown]
Research matrix and data collection methods for the parallel process evaluation.

### Sample size calculation

2.6

To detect a between-group difference over a 36-month period of 3 points on the RMDQ (i.e., the smallest worthwhile between-group difference that would justify the implementation of the intervention), with a standard deviation of 6 [49], a power of 85%, an alpha of 2.5%, a crossover rate of 15%, and allowing for a drop-out of up to 25%, a total of 318 patients are needed (i.e., 159 in each group) [50]. To detect a between-group difference of 15% over 36 months for the other co-primary outcome (physical activity), i.e., average number of steps with a standard deviation of 2448 steps [51], a power of 85%, an alpha of 2.5%, cross-over rate of 15%, and allowing for a drop-out of up to 25%, a total of 302 patients are needed. Therefore, 318 patients will be recruited.

### Statistical analysis

2.7

Data will be analysed in Rstudio. Primary analyses will be conducted according to the intention-to-treat principle and secondary analyses based on a per-protocol approach. Descriptive statistics will be used to describe baseline characteristics of the study population. Missing data for all outcomes and cost measures will be imputed using Multivariate Imputation by Chained Equations. All statistical tests will be two-tailed. Statistical significance for the co-primary outcomes is set at p < 0.025 to account for multiple testing.

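### The fixed 0.025 threshold for each co-primary outcome is valid, but Holm's procedure is uniformly more powerful at the same 5% family-wise error

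*Protocol article*

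**What the plan says.** The protocol names two co-primary outcomes: "The co-primary outcomes are physical functioning and physical activity (i.e., average steps per day over 7 days"). Under Statistical analysis it states "All statistical tests will be two-tailed" and "Statistical significance for the co-primary outcomes is set at p < 0.025 to account for multiple testing".

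The Sample size calculation section uses the same level. The RMDQ calculation starts "To detect a between-group difference over a 36-month period of 3 points on the RMDQ", continues "with a standard deviation of 6 [49], a power of 85%, an alpha of 2.5%, a crossover rate of 15" percent, and ends "allowing for a drop-out of up to 25%, a total of 318 patients are needed (i.e., 159 in each group"). The steps calculation uses the same alpha, power, crossover and drop-out, and gives 302.

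The article mentions no step-down, hierarchical or alpha-recycling rule. Nowhere does it require both outcomes to succeed.

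**The concern.** Under a fixed split, the second outcome stays at 0.025 even after the first has been established. Once one null hypothesis has been rejected, only one remains, and it can be tested at the full 5% without exceeding the family-wise limit. The fixed rule leaves that alpha unused.

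A possible result shows what is at stake. With RMDQ p = 0.004 and steps p = 0.035, the planned rule reports steps as not significant. Holm, which respects the same 5% limit, would accept both. The Background section presents functioning and activity together as the main aims of the intervention, so a conclusion on both outcomes is of real interest, and that is where the power is lost.

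**Working it through.** **Inputs from the protocol.** Two outcomes; two-sided alpha 0.025 each; power 85%; RMDQ difference 3, SD 6; crossover 15%; drop-out 25%; total 318.

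**Inputs assumed.** The two test statistics are bivariate normal. Their correlation, in the direction of benefit, is not given and is varied from 0 to 0.8. Each outcome is taken to have exactly 85% power at 0.025.

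**Step 1. Reproduce the plan's figure.**
- z(0.9875) + z(0.85) = 2.2414 + 1.0364 = 3.2778.
- Per arm: 2 × (6 × 3.2778 / 3)² = 85.95.
- Crossover: 85.95 / 0.85² = 118.97.
- Drop-out: 118.97 / 0.75 = 158.6, so 159 per arm and **318** in total.
- Two-sided 0.05 would give only 266–268, so the trial was sized on the fixed 0.025 threshold.

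**Step 2. Type I error.**
- Fixed split: at most 0.025 + 0.025 = 0.05; under independence 1 − 0.975² = 0.0494.
- Holm, both nulls true: an error needs the smaller p-value to fall below 0.025, which is the same event as under the fixed split. The error rate is therefore identical.
- Holm, one null true: a false rejection needs that p-value to be below 0.05 at most, so the rate is at most 5%.
- Neither argument uses the correlation.

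**Step 3. Both effects as planned.** The mean of each test statistic is 3.2778. Power is 85.0% at 0.025 and Φ(3.2778 − 1.9600) = 90.6% at 0.05, a gap of 5.62 points. Under independence:
- One given outcome with Holm: 0.85 + 0.0562 × 0.85 = 89.8%.
- Both, fixed split: 0.85² = 72.3%.
- Both, Holm: 0.7225 + 2 × 0.85 × 0.0562 = 81.8%.

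Across correlations, from the bivariate normal distribution:

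| Correlation | One given outcome: fixed → Holm | Both: fixed → Holm | At least one: either rule |
|---|---|---|---|
| 0 | 85.0 → 89.8% | 72.3 → 81.8% | 97.8% |
| 0.3 | 85.0 → 89.3% | 74.2 → 82.7% | 95.9% |
| 0.5 | 85.0 → 88.9% | 75.8 → 83.6% | 94.2% |
| 0.8 | 85.0 → 88.2% | 79.1 → 85.5% | 90.9% |

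The last column is the same for both rules because their first step is the same.

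**Step 4. Steps effect half as planned.** The mean of the steps statistic is 3.2778 / 2 = 1.6389. Its power is 27.3% at 0.025 and 37.4% at 0.05. Under independence:
- Steps with Holm: 0.273 + 0.85 × (0.374 − 0.273) = 35.9%. This reaches 37.3% at correlation 0.8.
- RMDQ with Holm: 0.85 + 0.0562 × 0.273 = 86.5%, a gain of 1.5 points. The gain is close to nil at correlation 0.8.

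**Step 5. Only RMDQ has an effect.** The false rejection rate for steps is 2.5% under the fixed split. Under Holm and independence it is 0.025 + 0.85 × 0.025 = 4.6%. It falls to 3.9% at correlation 0.8, so it stays within 5%.

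**Sensitivity to the steps input.** The reference mean behind the 15% difference is not stated, so 302 cannot be reproduced independently. Read backwards, it implies a difference of about 1,255 steps. With that difference and 318 patients, steps has 86.9% power at 0.025. Power for both then rises from 74.0% to 83.2% (correlation 0), from 77.3% to 84.8% (0.5) and from 80.4% to 86.5% (0.8). The gains are of the same size.

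**The case against.** The strongest defence is that nothing here is wrong. The split is prespecified, valid and consistent with the sample size, and each outcome meets its own 85% target. No passage sets a target for winning on both, so the largest gain concerns a goal that the protocol never states. All of this stands. A reader might infer that the fixed threshold inflates error or leaves the trial underpowered. The protocol's own figures show neither.

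A second objection is that the gain is a best case. This is partly right. The RMDQ gain depends on steps passing 0.025 first. It shrinks to 1.5 points or less with a half-size steps effect, and almost disappears with no steps effect. The Discussion itself expects some attenuation, because control participants may change their lifestyle independently. But the weaker outcome still benefits: steps power rises by about 9 to 10 points in that scenario.

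A third objection is to calling the gain free, and this stands too. No patients are added and the family-wise limit holds, but the false rejection rate for a single null outcome rises above 2.5%. Intervals are also less tidy. With steps p = 0.035, Holm rejects while a 97.5% interval includes zero. Under the fixed rule, p < 0.025 and a 97.5% interval always agree, which is a legitimate reason to prefer simplicity.

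Finally, Holm needs one p-value per outcome, and the Primary and secondary outcomes section describes both an overall 36-month difference and differences by time point. The present threshold needs the same choice, so this does not favour either rule. The choice may also be settled in an analysis plan that is not shown.

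**Conclusion.** This is an efficiency improvement to a sound rule. It does not correct an error. At 318 patients and the same 5% family-wise limit, Holm adds about 3 to 5 points of power per outcome and about 6 to 10 points for both, if both effects are as planned. It adds nothing to the chance of at least one success. The gain for each outcome depends on how often the other one passes 0.025.

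The type I error result holds under any correlation. The power figures rest on normal test statistics, 85% power per outcome at 0.025, and an assumed correlation between 0 and 0.8. The recommendation also assumes that success on either outcome is enough. Splitting alpha to account for multiple testing implies this: if both outcomes had to succeed, no split would be needed, and Holm would not be the right remedy.

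**What to change.** Replace the fixed threshold with a sentence such as: *The two co-primary outcomes, each represented by one prespecified primary test, will be tested with Holm's procedure at a family-wise two-sided 5% level: the smaller p-value against 0.025 and, if significant, the other against 0.05.*

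Report Holm-adjusted p-values as the decision rule: twice the smaller p-value, and for the other outcome the larger of its own p-value and that doubled value (each capped at 1). In the example these are 0.008 and 0.035, both below 0.05. State that the confidence intervals are descriptive and may not match the Holm decision.

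Keep 318 patients and the 85%-at-0.025 calculation as the planning figure.

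The cost is one or two sentences. Recruitment, measurements and models do not change. The stated drawbacks are the higher false rejection rate for a single null outcome (still within 5%) and the possible mismatch with intervals. The change should be recorded before any outcome data are compared between arms. Recruitment is planned to December 2026 with 36 months of follow-up, which leaves time for this.

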#### Primary and secondary outcomes

2.7.1

Linear mixed models with at least a two-level structure (i.e., time clustered within patients) will be used to analyse both co-primary outcomes; i.e., the difference in physical functioning and mean number of steps over a 7-day period during the 36-month treatment and follow-up period. The necessity of adding a third level (i.e., hospital) will be assessed using the −2 log-likelihood test. Time-by-group interaction terms will be used to detect differences between the groups at the various time points. Analyses will be adjusted for baseline confounders.

Secondary outcomes will be assessed using linear and logistic mixed models (depending on the nature of the dependent variable) using the same procedures as described above. Subgroup analyses will be performed to assess potential differences in outcome measures between people with different socio-economic status and the severity of LBP. Participants will be dichotomized into moderate or severe disability due to LBP based on a cut-off value of 40% on the RMDQ [52]. A RMDQ score of ≥40% (10 out of 24) indicates severe disability, while a score of <40% (9 out of 24) indicates moderate disability due to LBP. To test potential biases due to deviations from the intended intervention (e.g., crossovers), a per-protocol analysis will be performed in addition to the main intention-to-treat analysis.

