#### Experimental group: Combined lifestyle intervention

2.3.1

The experimental group will follow one of five nationally-registered combined lifestyle interventions (i.e., BeweegKuur, Coaching op Leefstijl (CooL), SLIMMER, Samen Sportief in Beweging (SSIB) or X-Fittt), integrated into standard care for LBP, according to Dutch clinical guidelines for LBP [11,12,[20], [21], [22]]. The overall aim of the combined lifestyle intervention is to counsel participants who are obese or overweight to help them achieve a healthier lifestyle. For the purpose of this study, the intervention was delivered by physiotherapists who are additionally certified as lifestyle coaches through a accredited training programme. This training includes formal education, supervised practice, and competency assessment in behaviour change techniques. The intervention is based on the Dutch combined lifestyle intervention (GLI), in which motivational interviewing is the primary behaviour change technique, supplemented by goal setting, action planning, and problem solving. These techniques are applied as part of routine clinical practice by certified lifestyle coaches. The programs follow a personalised approach, guiding participants to explore their current lifestyle habits and how these affect their well-being, and set goals to adopt healthier behaviours. They are stimulated to take responsibility and remain in charge of their personal goals. The intervention spans two years. During the first six to twelve months, sessions focus on identifying unhealthy behaviours related to physical activity, diet, sleep, and stress, and on supporting participants in making sustainable lifestyle changes. The remaining months of the program emphasize goal monitoring and the maintenance of newly adopted lifestyle habits. The program consists of both individual and group sessions; however, the exact contact moments, frequency, and specific content or structure of the sessions will differ between the various combined lifestyle interventions.

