#### Control group: Usual care

2.3.2

The control group will receive care as recommended by the medical specialist, which may range from a watchful waiting approach to referral for physiotherapy, exercise therapy or general practitioner care, in accordance with current Dutch guidelines for LBP according to the Royal Dutch Society of Physiotherapy [11] and the Dutch College of General Practitioners [12]. It may also involve re-entry to the hospital after failed treatment in primary care. Similar to the intervention group, usual care follows a guideline-based, predominantly active approach that may include education and exercise therapy. However, it is delivered in routine clinical practice without the structured, multidisciplinary lifestyle coaching programme, predefined two-year follow-up structure, or systematic use of behaviour change techniques that are central to the intervention group.

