### Randomisation, blinding and treatment allocation

2.4

Participants will be randomised with a 1:1 ratio using a central computer-generated randomisation program by an independent researcher not involved in the study. A block randomisation approach (alternating block sizes of 6 and 4) will be used. Randomisation will be conducted after providing informed consent and completing the baseline measurement. Participants will be informed orally about their allocation. Treating medical specialists and general practitioners will be informed about the allocation of the participant. In this type of study, blinding patients and healthcare providers is not feasible; however, data analysis will be conducted by an investigator who is blinded to group assignments.

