A major strength is that the intervention builds on the existing combined lifestyle interventions and other existing interventions recommended in national guidelines, which increases the chance of successful implementation when the intervention is deemed (cost-)effective. However, since the combined lifestyle intervention is not currently tailored to our patient group (i.e., people with persistent LBP), a process evaluation is needed to gain insight into the implementation and usefulness of its various components. In addition, the inclusion of multiple distinct combined lifestyle intervention programs to better reflect routine clinical practice may lead to variability within the experimental intervention arm, potentially introducing heterogeneity in the outcomes. Furthermore, the control arm receives usual care without restrictions, aside from being asked to not participate in combined lifestyle interventions. Consequently, control participants may still engage in lifestyle modifications independently, including consulting health professionals such as dieticians or personal trainers. This may attenuate the observed differences between the intervention and control arm. In response, healthcare usage (e.g., medical, allied health, medication and other) will be systematically recorded in both study arms.

A potential limitation could be that participants may perceive the 36-month duration of the trial as too long. To mitigate this, questionnaires and measurements have been carefully selected to minimize participant burden. Additionally, to maintain engagement throughout the study, participants will receive postcards on special occasions (e.g., birthdays and holidays) and periodic updates.

In summary, the Back2Health trial will provide much needed insight in the (cost-)effectiveness of a comprehensive, personalised treatment integrating lifestyle and clinical factors) for people with chronic non-specific LBP who are also overweight or obese, compared to a usual care approach. The trial will evaluate its impact on clinical outcomes, including self-reported physical functioning and objectively measured physical activity. Integrating lifestyle into the treatment of low back pain may also provide an opportunity to address lifestyle-related comorbidities that co-occur in this population, contributing to broader improvements in health and wellbeing.

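### The primary model names only hospital as an extra level, so it would understate standard errors if trial participants who share a lifestyle coach or session group have correlated outcomes

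*Protocol article*

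**What the plan says.** Section 2.7.1 sets out the primary model: "Linear mixed models with at least a two-level structure (i.e., time clustered within patients) will be used to analyse both co-primary outcomes". The one candidate for a further level follows: "The necessity of adding a third level (i.e., hospital) will be assessed using the" −2 log-likelihood test.

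Section 2.4 makes the individual the unit of allocation: "Participants will be randomised with a 1:1 ratio using a central computer-generated randomisation program". Under section 2.2, patients are recruited in hospitals and are being referred back to primary care.

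Section 2.3.1 describes the experimental arm. "The experimental group will follow one of five nationally-registered combined lifestyle interventions", and "The program consists of both individual and group sessions". On the provider it says that "the intervention was delivered by physiotherapists who are additionally certified as lifestyle coaches". The programme lasts two years.

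Section 2.3.2 says of usual care that "it is delivered in routine clinical practice without the structured, multidisciplinary lifestyle coaching programme", although control patients may be referred to physiotherapy or exercise therapy.

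The sample size paragraph (section 2.6) lists effect, standard deviation, power, alpha, crossover and drop-out, and no allowance for clustering. Section 2.7.2 provides for clustered data in the economic analysis if needed, without saying what the cluster is.

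**The concern.** This is an individually randomised trial in which one arm is treated through shared providers and, in part, shared groups. Such a design is partially nested. Participants with the same coach or session group may end up more alike than participants with different ones, and in the experimental arm that correlation adds to the variance of the arm mean.

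The plan considers clustering and picks hospital. That level does a different job. Each hospital contributes patients to both arms, so a hospital effect common to both largely cancels from the treatment contrast. Variation between coaches or groups arises after randomisation, in the experimental arm, and does not cancel. A model with patient and hospital levels treats experimental-arm patients within a hospital as independent, whether or not they share a coach.

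At stake are the size of both co-primary tests, the width of their confidence intervals and the stated power. The treatment estimate itself is not biased by this.

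**Working it through.** **1. Reproduce the plan's sample size.** Inputs from sections 2.6 and 2.7: difference 3 RMDQ points, SD 6, power 85%, two-sided alpha 2.5%, crossover 15%, drop-out 25%.

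- Normal quantiles: 2.2414 (two-sided 2.5%) and 1.0364 (85%); sum 3.2778.
- Per arm: 2 × (6 × 3.2778 / 3)² = 85.95.
- Crossover: 85.95 / 0.85² = 118.97.
- Drop-out: 118.97 / 0.75 = 158.6, rounded up to 159 per arm, or 318 in total.

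This matches the stated figure exactly, so 318 assumes independent outcomes.

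**2. Effect of clustering in one arm.** Let m be the number of *trial participants* per coach or group and ICC the correlation of their outcomes. The article gives neither, so the values below are assumptions.

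- Design effect in the experimental arm: DE = 1 + (m − 1) × ICC. In the control arm it is taken as 1.
- Variance factor for the contrast: v = (1 + DE) / 2. The true standard error is √v times the one the model reports.
- True size of the nominal 2.5% test: 2 × [1 − Φ(2.2414 / √v)].
- Power when the standard error is correct: Φ(3.2778 / √v − 2.2414).

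| m | ICC | DE | v | √v | True size | Power |
|---|---|---|---|---|---|---|
| 1 | any | 1.00 | 1.000 | 1.000 | 2.5% | 85% |
| 2 | 0.01 | 1.01 | 1.005 | 1.002 | 2.5% | 84.8% |
| 2 | 0.02 | 1.02 | 1.010 | 1.005 | 2.6% | 84.6% |
| 3 | 0.05 | 1.10 | 1.050 | 1.025 | 2.9% | 83% |
| 6 | 0.02 | 1.10 | 1.050 | 1.025 | 2.9% | 83% |
| 10 | 0.05 | 1.45 | 1.225 | 1.107 | 4.3% | 76% |
| 10 | 0.10 | 1.90 | 1.450 | 1.204 | 6.3% | 68% |

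Confidence intervals are too narrow by 1 − 1/√v: about 2% at m=6, ICC 0.02 and about 10% at m=10, ICC 0.05. The size column depends only on m and ICC, so it applies to steps per day as well, with that outcome's own ICC. The power column is for the RMDQ.

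**3. Does the hospital intercept help?** By the argument above it should not. A small simulation under no treatment effect (10 hospitals spanning both arms, hospital intercept fitted, about 270–280 usable fits per setting) points the same way. At m=12, ICC 0.05 the mean model standard error was 0.768 against an empirical SD of 0.890, with about 5.4% rejections. The run without clustering gave 0.769 against 0.825 and 3.0%, so noise is appreciable. I rely on the formula and take the simulation only as agreeing in direction.

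**The case against.** Several points on the other side stand.

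- **Cluster size may be small.** A reader might infer that the standard errors *will* be too small. The article does not show that. With 159 experimental-arm patients, m=6–10 implies only about 16–27 coaches or groups (159/10 = 15.9; 159/6 = 26.5). Recruitment is nationwide over two years and spread over five programmes that are open to eligible adults in general, so a session group may hold few trial participants. At m of 1 to 3 the error is small.
- **The model is not closed.** A reader might infer that hospital is the only level *permitted*. The text sets two levels as a minimum, and an analysis plan that is not shown could add more. What can be said is that hospital is the only further level *named*. That is still a stated choice, and it names the recruiting unit where the treating unit is the one at issue.
- **Controls also see providers.** It is too strong to say that provider clustering exists in one arm only, since usual care can include physiotherapy. What is confined to the experimental arm is the structured coaching and its group sessions.
- **Programme heterogeneity is a different matter.** The Discussion concedes that using several programmes "may lead to variability within the experimental intervention arm, potentially introducing heterogeneity in the outcomes". That concerns differences between programmes and is not evidence of correlation within coach or group.
- **Power may not fall.** The 318 takes no credit for repeated measures or baseline adjustment. Suppose the baseline RMDQ is in the model with correlation 0.5 to the outcome (an assumption), and the between-coach variance is unaffected. At m=10, ICC 0.05 the contrast variance relative to plan is then 0.75 + 0.225 = 0.975, and power is Φ(3.2778/√0.975 − 2.2414) = 86%. This answers the power point but not the size point: the model would report a variance of 0.75 where the true one is 0.975, and the test would still be too liberal.

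**Conclusion.** The point holds in conditional form. The named extra level does not match the level at which the experimental treatment is delivered. If trial participants share coaches or groups and their outcomes correlate, both co-primary tests are anti-conservative and the hospital term does not repair this.

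The size of the problem rests wholly on m and ICC, which the article does not give. Over the assumed range it goes from negligible (2.5–2.6% at m=2, ICC 0.01–0.02) to material (4.3% against a nominal 2.5% at m=10, ICC 0.05). The matching power, with no other gains, is about 85% down to 76%, and I would not present that as an expected loss given the uncredited baseline adjustment. The documents do not support calling the analysis invalid. They support specifying it better while the identifiers can still be collected.

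**What to change.** 1. Record coach and session group for each experimental-arm participant. Recruitment is planned to December 2026 and the programme lasts two years, so this is easier during delivery than afterwards.
2. Prespecify a partially nested primary model for both co-primary outcomes: a random coach/group effect in the experimental arm, each control patient treated as a singleton, and small-sample degrees of freedom (Satterthwaite or Kenward-Roger). Keep the term without a significance pre-test, because a likelihood-ratio test with few clusters has little power to detect it. Arm-specific residual variance, and keeping hospital in without a pre-test, are sensible options but partly matters of preference.
3. Use the same cluster definition in the economic analysis.
4. State the power over an assumed range of ICC and of trial participants per coach or group.

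The cost is the identifier fields, some analysis-plan text, slightly wider intervals where clustering is present, and a stated power that may be lower. No extra patients are needed. If almost every participant turns out to have a different coach and group, the random effect cannot be estimated separately from patient-level variation, so the plan should say in advance how the model reduces in that case. Little is lost then, because the variance factor is close to 1.
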